### Data sharing

Data will be available to share on reasonable request to the data custodian following relevant local ethical approvals. Each site will be responsible for uploading their data to Research Electronic Data Capture (REDCap).^15^ Each site will only be able to add data for their own patients and will not be able to see or modify data for any other site. The central study team will receive anonymised data only; thus, a data monitoring committee is not required.

### Sample size calculation

This multicentre study will take place over 1 week (each site will collect data for 1 week during a 2-month study period), aiming to recruit at least 1500 participants. The sample size is calculated for detection of patient-experienced intraoperative pain, which is estimated to be 15% based on single-centre pilot study data, with a 95% CI and a margin of error of ±3%. This gives a total of approximately 676 participants.

However, since there will be multiple centres in the study, a design effect has been used to account for between site variation and within site clustering. The design effect is 1+ICC*(n−1) and n is the number of subjects per cluster. As we do not have empirical data for ICC, we have used 2 as the design effect. So, the n is 676*2, giving a total sample size of approximately 1352 participants. We estimate up to 10% will have incomplete data within their CRFs. At 6 weeks, we anticipate approximately 70% of participants will be followed up. This therefore gives a total sample size of 1500 participants with complete baseline, 24 hours and 6-week follow-up data.

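### The base sample size of 676 does not follow from 15% incidence, a 95% CI and ±3%, which give 545, and the error carries into 1352 and 1500

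*Protocol article*

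**What the plan says.** All the relevant text is in the protocol article, under Analysis plan, Sample size calculation. The quantity to be estimated is the incidence of patient-experienced intraoperative pain, which the Outcome measures section names as the primary outcome. The planning inputs are an incidence "which is estimated to be 15% based on single-centre pilot study data", together with a precision requirement "with a 95% CI and a margin of error of ±3" per cent. The result is given directly: "This gives a total of approximately 676 participants".

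The section then allows for clustering: "As we do not have empirical data for ICC, we have used 2 as the design effect". The next step is "So, the n is 676*2, giving a total sample size of approximately 1352 participants". It goes on: "We estimate up to 10% will have incomplete data within their CRFs". The final target is 1500. The section names no interval method, power, finite-population correction or second incidence.

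**The concern.** The section prints its inputs and its result and says that one gives the other. They do not agree. Because it is an explicit statement, this is not a detail that a condensed article leaves to a fuller protocol or SAP.

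This is the only sample size calculation in the document, and it serves the primary outcome. A reader who tries to reproduce it cannot tell whether the study was really sized for 15% or for nearly 20%, or for ±3 points or about ±2.7. The choice of incidence matters because the Introduction reports published rates from 1.7% to 33%, and the 15% is attributed to the study's own pilot. If 676 came from an incidence near 20%, the pilot-based assumption is misreported. If 15% is right, the stated precision is not what the planned numbers deliver.

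**Working it through.** **Inputs (all from Sample size calculation).** Incidence p = 0.15; two-sided 95% confidence, z = 1.96; half-width d = 0.03; design effect 2; up to 10% incomplete data; stated results 676, 1352 and 1500.

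**1. Attempt to reproduce 676.** The usual precision formula for one proportion is n = z² p(1 − p) / d².

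n = 3.8415 × 0.15 × 0.85 / 0.0009 = 3.8415 × 0.1275 / 0.0009 = 544.2, so 545.

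The stated figure is not reproduced: 676 / 545 = 1.24.

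**2. Other interval methods.** Smallest n with a 95% half-width of at most 3 points at 15%:

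| Method | n |
|---|---|
| Wald | 545 |
| Wilson | 545 |
| Logit | 547 |
| Agresti-Coull | 548 |
| Wald, continuity-corrected | 578 |
| Clopper-Pearson (exact) | about 572 to 578, by rounding of the count |
| Wilson, continuity-corrected | about 573 to 579, by rounding of the count |

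Using z = 2 in place of 1.96 gives 567. A finite-population correction lowers n. A one-sample test of 15% against 12% or 18% at 80% or 90% power needs at least 824. None of these gives 676.

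**3. What 676 would correspond to.** Solving for one input at a time:

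- Margin, at 15% and 95%: 1.96 × √(0.1275 / 676) = 0.0269, or ±2.69 points.
- Incidence, at 95% and ±3 points: p(1 − p) = 676 × 0.0009 / 3.8415 = 0.1584, so p = 0.197. An incidence of exactly 20% gives 683.
- Confidence, at 15% and ±3 points: z = √(676 × 0.0009 / 0.1275) = 2.184, or about 97.1%. Confidence of exactly 97% gives 668.

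**4. Later steps.** These are sound once 676 is accepted: 676 × 2 = 1352, and 1352 / 0.9 = 1502, the apparent source of 1500. The fault therefore enters at the first step and is inherited.

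| Step | As stated | From the stated inputs |
|---|---|---|
| Base | 676 | 545 |
| × design effect 2 | 1352 | 1090 |
| ÷ 0.9 for incomplete data | 1502 (given as 1500) | 1211.1, so 1212 |

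**5. What 1500 delivers at 15%.** With 10% incomplete, 1500 × 0.9 = 1350 are analysable.

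- At design effect 2: 1.96 × √(2 × 0.1275 / 1350) = 0.0269, or ±2.7 points.
- Largest design effect that still gives ±3 points: 1350 / 544.2 = 2.48.

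**The case against.** The best defence is that the discrepancy does no harm. The planned number exceeds what ±3 points needs at design effect 2. The target is worded as a minimum, and recruitment closed on 17 May 2025 (Key study dates). No estimate or analysis of the primary outcome changes. All of this stands, and it limits the consequence to one of reporting.

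A second defence is that an unstated conservative method may lie behind 676. If only the upper confidence limit had to lie within 3 points of 15%, an exact interval would need about 640 (586 to 695 with whole-number counts, depending on rounding and on whether all larger n must also comply). A continuity-corrected Wilson limit would need about 663 (606 to 715 on the same basis). So 676 falls within reach of such a rule. But the section states a symmetric margin, which reads as a half-width, and names no such method. The possibility is a reason to let the sponsor state the method; it does not make the printed statement correct.

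A third point is that the steps after 676 are arithmetically right. That is true, and the claim about 1352 and 1500 is only that they inherit the first error.

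Finally, the anticipated 70% follow-up at 6 weeks is mentioned but not applied in reaching 1500. That is a separate matter that does not depend on 676, and it adds no weight here.

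**Conclusion.** The concern holds. On the stated 15%, 95% and ±3 points, the base sample size is 545. The stated 676 is 24% above that, and 17% above the largest value (579) from any two-sided 95% half-width method tried. The figures 1352 and 1500 rest on it; 1090 and 1212 would follow from the stated inputs.

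The error is conservative. Taking the 15% incidence, the design effect of 2 and the 10% loss as given, 1350 analysable women yield about ±2.7 points, better than the stated ±3. The fault is an internal contradiction in the primary planning calculation, not an undersized study. If 676 in fact came from an incidence near 19.7%, the planned margin is ±3 points with nothing to spare, and it is the 15% that needs correcting.

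**What to change.** If 15% and ±3 points are the intended inputs, correct 676 to 545 and 1352 to 1090, and show the step for incomplete data (1212). Otherwise, state the incidence, confidence level, margin and interval method that produce 676.

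In the first case, keep the recruitment target of 1500 and say what it provides for the primary outcome at 15% incidence with 10% incomplete data: about ±2.7 points at design effect 2, or ±3 points for any design effect up to about 2.5. The second form is the more useful, because the section itself says that the design effect of 2 has no empirical basis.

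The cost is one recalculation and a few changed words, with no effect on recruitment or data collection. The corrected figures should also be the ones carried into the results paper.

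### The 1500 described as having complete data to 6 weeks is the recruitment target; the plan's own follow-up figure leaves about 1050, or 900 to 945 if incomplete forms are also deducted

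*Protocol article*

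**What the plan says.** All the figures are in the protocol article under Sample size calculation. The section opens with the recruitment aim: "aiming to recruit at least 1500 participants". The size is set for patient-reported intraoperative pain, "estimated to be 15% based on single-centre pilot study data", "with a 95% CI and a margin of error of ±3" per cent. From this the article takes a base number: "This gives a total of approximately 676 participants".

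Clustering by site is handled with an assumed design effect: "As we do not have empirical data for ICC, we have used 2 as the design effect". The result is: "So, the n is 676*2, giving a total sample size of approximately 1352 participants".

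Two kinds of loss follow. Up to 10% of participants are expected to have incomplete forms, and "At 6 weeks, we anticipate approximately 70% of participants will be followed up". The section then concludes: "This therefore gives a total sample size of 1500 participants with complete baseline, 24 hours and 6-week follow-up data".

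Under Outcome measures, the primary outcome is pain as reported by the patient in CRF2, which is completed about 24 hours after surgery. The secondary outcomes at 6 weeks are positive screens for depression, anxiety and PTSD, and pain scores.

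**The concern.** One number, 1500, is used both for the people who enter the study and for the people with data at every time point up to 6 weeks. With about 30% expected to be lost by 6 weeks, it cannot be both. The word that links the conclusion to the inputs tells the reader that the 70% follow-up has been allowed for, and it has not.

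What is at stake is the number behind the 6-week outcomes. The Introduction names the physical and psychological impact of intraoperative pain as an aim, the fourth research question asks about longer-term outcomes, and the Inferential statistics section plans regression on them. A reader who relies on the sample-size section would expect these analyses to have 1500 participants, and might later judge the completeness of 6-week follow-up against that figure.

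**Working it through.** **Inputs** (all from Sample size calculation): base number 676; design effect 2; up to 10% with incomplete forms; about 70% followed up at 6 weeks; at least 1500 to be recruited.

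**Reproducing the plan's 1500**
- After the design effect: 676 × 2 = 1352, as stated.
- After the 10% allowance: 1352/0.90 = 1502, which rounds to the stated 1500.
- If 70% follow-up had been applied instead: 1352/0.70 = 1931.4, so 1932 recruits.
- If both had been applied: 1352/(0.90 × 0.70) = 2146.03, so 2147 recruits.

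The figure of 1500 is therefore reproduced as a number to recruit with the 10% allowance alone. It is not reproduced as a number with 6-week data.

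**What 1500 recruits give on the plan's own figures**

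| Quantity | Calculation | Result | Shortfall from 1500 |
|---|---|---|---|
| Complete forms, before any 6-week loss | 1500 × 0.90 | 1350 | 10% |
| 6-week data, 70% of recruits | 1500 × 0.70 | 1050 | 30% |
| 6-week data, both losses, independent | 1500 × 0.90 × 0.70 | 945 | 37% |
| 6-week data, both losses, no overlap | 1500 × (1 − 0.10 − 0.30) | 900 | 40% |

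The article does not say how the two losses combine, so the last three rows are a range. Conversely, 1500 participants with 6-week data would need 1500/0.70 = 2143 recruits, or 1500/(0.90 × 0.70) = 2381. Neither figure appears in the article.

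**Illustration of precision.** The article gives no expected proportion for a 6-week outcome. Borrowing 15% and the design effect of 2 from the primary outcome, purely as assumptions, the 95% half-width is 1.96 × √(2 × 0.15 × 0.85/n):
- n = 1500: ±2.6 points
- n = 1050: ±3.1 points
- n = 945: ±3.2 points

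**A side note on 676.** The usual formula gives 1.96² × 0.15 × 0.85/0.03² = 544.2, so 545 rather than 676. That is a separate matter. It errs on the large side and does not change this point.

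**The case against.** The strongest reply is that the size was set for the primary outcome, and that outcome is safe. It is collected in CRF2 at about 24 hours, and 1350 expected against 1352 wanted is no real loss. This stands. A reader might infer from the faulty sentence that the study is too small for its main question; the article's figures do not support that.

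A reader might also infer that the plan overstates the precision or power of the 6-week comparisons. The article states neither for any 6-week outcome; its ±3% belongs to intraoperative pain. There is no claimed precision or detectable difference to be wrong, and a power calculation would need a comparator rate that the article does not supply. Only the headcount is overstated. The precision figures in the working rest on a borrowed 15% and should not be written into the protocol as expected values.

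Two further replies do not rescue the sentence. The recruitment aim is a floor, so more may be recruited; but the sentence presents 1500 as the result of the stated inputs, and they do not give it. Nor can 1500 be read as completers with a larger number recruited, because the only recruitment figure given is 1500. A fuller protocol or analysis plan may hold more detail, but this is a wrong conclusion in the text shown, not an omission.

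Finally, the 10% refers to forms in general, and there are three of them. Assigning it to the first two only would go beyond the text, which is why 1050 is the main figure and 945 and 900 depend on stated assumptions.

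**Conclusion.** The concluding sentence is wrong as written. The 1500 is a recruitment target that contains the 10% allowance only. On the plan's own figures the expected number with 6-week data is about 1050, about 945 if incomplete forms are a further independent loss, and 900 if the two losses do not overlap. That is 30 to 40% below the number stated for the 6-week secondary outcomes.

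The range assumes exactly 1500 recruits, 70% follow-up and, for the two lower values, the full 10% loss. The primary outcome is unaffected. On the illustrative assumptions, the half-width for a 6-week proportion widens by about half a percentage point, which is modest.

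This should be corrected, but it does not endanger the main objective. Nor does it follow that recruitment should have been 2143 to 2381: those figures apply only if 1500 completers were a requirement, and the article gives no separate 6-week target from which such a requirement would come. Key study dates also records that recruitment closed on 17 May 2025, so the remedy lies in the description.

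**What to change.** In Sample size calculation, describe 1500 as the number to recruit, derived from 1352 with the 10% allowance. Replace the concluding sentence with one saying that, at the anticipated 70% follow-up, about 1050 of 1500 recruits are expected to have 6-week data. If the 10% is meant to apply to those participants as well, say so and give about 945 (independent losses) or 900 (no overlap). Base any later statement of 6-week precision on that number, with an expected proportion chosen and justified for the outcome concerned.

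The cost is a sentence or two. Recruitment, data collection and the primary analysis do not change. The one downside is a less favourable stated figure for the 6-week outcomes.

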### Study management

The day-to-day running of the study will be performed by the study coordinator, in conjunction with the chief investigator and core members. A study management group will meet monthly providing updates on the delivery of the study. Finally, a study oversight board, independent of the study team, will meet to provide independent advice and guidance.

### Patient and public involvement

The themes of this study were prompted by a personal experience of pain during CB.^16^ We have sought public and patient involvement and input from a community-based parent group in North London, comprised people who have given birth at UCLH hospitals within the last 2 years. Two patient/public representatives with relevant experience are members of the study group, playing an equal part in decision-making to clinician and scientist members. The study documents, including the development of the protocol, participant information leaflet, participant information poster, letters for participant and GP, consent form and all CRFs, have been co-designed and ratified with the study team and patient and public representatives.

### Ethics and dissemination

This study received ethical approval from the Leicester Health Research Authority and Care Research Wales, REC reference 24/EM/0084) on 24 May 24. The study received ethical approval from the Human Research Ethics Committee of Metro North Health in Australia on 25 March 2024 (REC Ref HREC/2024/MNHA/103767). The trial is registered with the ISRCTN (ISRCTN15269213, https://doi.org./10.1186/ISRCTN15269213). The results of the study will be reported in accordance with the STROBE statement.

Data for the patient cohort will be first collected on paper CRFs before being transcribed onto electronic CRFs via a dedicated, secure online web tool. Completed paper CRFs were held in a secure location accessible by the local researchers in accordance with Good Clinical Practice guidelines and local information and research governance frameworks.

Data will be entered electronically via a secure, encrypted connection onto an online portal hosted by University College London. The software used for data capture will be REDCap (http://www.project-redcap.org), a secure web application for building and managing online surveys and databases. Access to the web tool is limited to local site Principal Investigators and two other users at local sites that are nominated by local Principal Investigtors. These were password-protected user accounts, and encrypted server connected using Hypertext Transfer Protocol Secure. No local site will have access to any other site information other than their own. An anonymised dataset will be uploaded onto the centralised study database via University College London’s (UCL) REDCAP web-based portal hosted on secure UCL servers. No personal identifiable data from the hospital CRF paperwork will be uploaded to REDCap.

The study is compliant with the requirements of General Data Protection Regulation (2016/679) and the UK Data Protection Act (2018). All investigators and study site staff will comply with the requirements of the General Data Protection Regulation (2016/679) with regards to the collection, storage, processing and disclosure of personal information, and will uphold the Act’s core principles.

The results will be disseminated via conference presentations, peer-reviewed academic journals and reports prepared for patients, the public and policy makers.

### Dissemination and transparency policy

We intend to present the results of SONAR1 in peer-reviewed scientific journals and at medical conferences. Local Principal Investigators and other investigators will be individually named as collaborators for their support. In addition to academic publications, we will provide specific summary reports for the following groups:

Partner Colleges—this will include the Royal College of Anaesthetists, Royal College of Obstetricians and Gynaecologists and Australian and New Zealand College of Anaesthetists and Royal Australian and New Zealand College of Obstetricians and GynaecologistsPatients and the Public—our lay representatives will provide support in our dissemination to the non-medical audience.Participating NHS Trusts and Health Boards—all NHS chief executives of all participating organisations will be sent a summary of the key findings.

The study investigators and steering committee have agreed a policy for authorship and contributor status for all manuscripts which arise from this study.

### Conclusions

SONAR1 will use a multi-centred prospective study design and PROMs to obtain detailed information from a comprehensive sample of patients having a CB in the UK and Australia to investigate the incidence of intraoperative pain, neuraxial failure and the impact on short and medium-term outcomes for patients.
